**Fig. 2 Fig2:**
[figure not shown]
Patient flow for screening and treatment. Blue boxes and darker arrows indicate the community components that will only be present in model 2. *Note that result return will be delayed for community-screened women; same-day results will only be possible for women screened at facilities. HSA, health surveillance assistant

Educational talks and self-sampling instructions can be given by HSAs, nurses, mid-level providers, and doctors, while only nurses, mid-level providers, and doctors can perform VIA and thermal ablation. All clinical staff will undergo protocol-specific training sessions before conducting duties related to the new interventions. They will also receive weekly visits from the study’s clinical mentors (either clinicians or nurses), who will observe the clinical staff using observation checklists and collect data from the clinic and HSA registers on a monthly basis to promote adherence to study protocols and accurate data entry into the registers.

### Assessments

#### Overview of study components

Details of assessments, including how they align with objectives, are shown in Table 2. For the assessments with specific eligibility criteria for participants, the criteria are listed in the “Participants” column in the table. Most quantitative data collection will be conducted using the Open Data Kit (ODK) software on electronic tablets.

#### Endline Household Survey

The Endline Household Survey, conducted at months 13–15 after implementation, will be the primary tool to assess the uptake of CCSPT and FP services among women in the catchment areas of the health facilities. Households will be sampled in a two-stage sampling design. Stage 1 will include a random sample of enumeration areas (EAs) from all of the facilities’ catchment areas. This random sample will be selected with the number of EAs proportional to the size of the catchment area. In each selected EA, we will undertake a household listing to create a sampling frame of households for the survey. In stage 2, a random sample of households will be selected. Our target sample size is up to 8000 women aged 15–50 years from the 16 health facility catchment areas. The age range is intended to include women most likely to utilize FP services, as well as those in the target range for CCSPT. With the expectation of ~1.1 women aged 15–50 in our households, the sample will include ~8000 households selected from 266 EAs selected proportionally from facility catchment areas (randomly selecting ~30 households/EA). Parental consent will be obtained for participants 15–17 years old, as described in the “Ethical considerations” section. If a randomly sampled woman does not consent for the survey, she will be replaced with another randomly selected woman from her EA.

Women aged 15–50 years will be eligible to participate in the interviewer-administered survey, provided that they have not had their cervix removed. The survey will cover demographic information, reproductive health information, HIV status, distance to the nearest health facility, prior FP use, FP use during project implementation, prior CCSPT services received, and CCSPT services received during project implementation.

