**Methods:**

We designed a cluster randomized feasibility trial to determine the effectiveness, acceptability, appropriateness, feasibility, and budget impact of two models for integrating a HPV-based CCSPT program into family planning (FP) services in Malawi: model 1 involves only clinic-based self-sampled HPV testing, whereas model 2 includes both clinic-based and community-based self-sampled HPV testing. Our algorithm involves self-collection of samples for HPV GeneXpert® testing, visual inspection with acetic acid for HPV-positive women to determine ablative treatment eligibility, and same-day thermal ablation for treatment-eligible women. Interventions will be implemented at 14 selected facilities. Our primary outcome will be the uptake of cervical cancer screening and family planning services during the 18 months of implementation, which will be measured through an Endline Household Survey. We will also conduct mixed methods assessments to understand the acceptability, appropriateness, and feasibility of the interventions, and a cost analysis to assess budget impact.

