## Methods/design

### Aims and objectives

Our aim is to compare the effectiveness, acceptability, appropriateness, feasibility, and budget impact of integrating self-sampled HPV testing into FP services via clinics only versus including community-based screening.

Our specific objectives are as follows:
Compare the effectiveness of our two models on uptake of CCS and FP services among eligible women in the catchment areas of health facilities assigned to the two models. The effectiveness will be evaluated through analysis of an Endline Household Survey, which will be administered to randomly selected eligible women in the catchment areas of the health facilities at the end of project implementation.
We hypothesize that the proportion of eligible women who have received CCS services during the 12 months of project implementation will be higher among eligible women in the catchment areas of health facilities assigned to model 2 than in model 1.We hypothesize that the proportion of eligible women who have received FP services during the 12 months of project implementation will be higher among eligible women in the catchment areas of health facilities assigned to model 2 than in model 1.Assess the acceptability, appropriateness, and feasibility of the two models among key stakeholders, including providers, facility management teams, and clients. These implementation outcomes will be evaluated through analysis of mixed methods assessments, including use of quantitative tools (Acceptability-Appropriateness-Feasibility Tool, Client Exit Survey) as well as qualitative interviews with providers, facility management teams, and clients.
We hypothesize that both models will be viewed as acceptable and appropriate by health care providers, facility management teams, and clients.We hypothesize that both models will be feasible in a variety of health facilities in Malawi.Estimate the cost and budget impact of each model compared to the standard-of-care (VIA and cryotherapy). These outcomes will be evaluated through analysis of structured observations during time-and-motion studies, the Workload Assessment Tool, and cost expenditures during implementation of the study.
We hypothesize that both models will be more cost-effective than the current standard-of-care for the number of cervical cancer case averted.We hypothesize that model 1 will be more cost-effective than model 2.

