### Design

This is a hybrid type 2 cluster randomized feasibility trial, with 16 health facilities in Malawi assigned to either a clinic-only or a clinic-and-community model for CCSPT. The study will take place over a period of 2.5 years, with a pre-implementation phase of 6 months, an implementation phase of 18 months, and a dissemination phase of 6 months (Fig. 1 and Table 1).

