### Sample size calculations

Sample size calculations were based on the ability to detect a difference in service uptake through the Endline Household Survey. As noted earlier, only 26.5% of Malawian women had been screened at least once in their lifetime as of 2015 with use of VIA for primary screening [3], which is much lower than the targeted rate of 80% set at the onset of Malawi’s Cervical Cancer Control Program in 2004 [16]. We estimated that with the introduction of HPV self-sampling in our clinic-only arm, at least 40–50% of eligible women in our facility catchment areas will be screened during our 18 months of implementation. We then estimated that with the addition of HPV self-sampling in the community to reach rural women, we would be able to approach Malawi’s targeted rate of 80% of eligible women screened in our clinic + community arm. Based on data obtained from potential facilities in Lilongwe and Zomba, we also estimated an average cluster size of 8000 eligible women per health facility and a coefficient of variation of the cluster sizes of 0.35. Finally, we estimated that our intra-cluster correlation coefficient (ICC) will be between 0.12 and 0.19, based on other similar studies performed in Malawi, where the ICC ranged from 0.004 to 0.20 [25, 26]. With 16 randomized facilities (8 per arm), we initially estimated that we would have at least 80% power to detect a difference of at least 25–30% between our 2 arms, even if the proportion of women screened in the clinic-only arm is as low as 40%. For example, if the clinic-only arm found that 40% of women had been screened, we would have 80% power to detect a difference if the clinic + community arm had screened at least 75% of women in their catchment areas.

However, after performing site selection and randomization, we learned that the two central/district hospitals selected could not be assigned to model 2 as their HSAs did not perform community-based services. Therefore, we dropped these 2 hospitals from our sample size calculations and decreased our average cluster size to 3400 eligible women accordingly. With an ICC of 0.15 and coefficient of variation of cluster sizes of 0.35, we will have at least 83% power to detect of difference of at least 30% between our 2 arms (with 7 facilities in each arm), even if the proportion of women screened in the clinic-only arm is as low as 40%. All power calculations were calculated in R (Version 3.5.1, clusterPower package).

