### Analysis plan

#### Endline Household Survey

Key outcomes from the Endline Household Survey include (1) the proportion of eligible women who have received CCS during the 18 months of study implementation, (2) the proportion of treatment-eligible women who received thermal ablation during the study period, and (3) the proportion of women aged 15–50 years who are using a modern FP method. These proportions will be calculated using descriptive statistics. Differences between the clinic-only and clinic-and-community models will be assessed via logistic regression, adjusted for district, facility size, and facility type. The regression model will account for health facility clustering, and analyses will be adjusted for the small number of clusters [28, 29].

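### Screening uptake is defined over 18 months in some places and 12 in others, and the survey at months 13–15 cannot observe the 18-month version

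*Protocol article*

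**What the plan says.** All of the following is current text in the protocol article.

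- **Abstract, Methods.** The primary outcome is "uptake of cervical cancer screening and family planning services during the 18 months of implementation", measured by the Endline Household Survey.
- **Analysis plan, Endline Household Survey.** The first key outcome is "the proportion of eligible women who have received CCS during the 18 months of study implementation".
- **Sample size calculations.** The clinic-only planning rate is that "at least 40–50% of eligible women in our facility catchment areas will be screened during our 18 months of implementation".
- **Aims and objectives.** The screening hypothesis concerns eligible women "who have received CCS services during the 12 months of project implementation". The family planning (FP) hypothesis has the same window: "received FP services during the 12 months of project implementation will be higher among eligible women".
- **Design.** The study has "an implementation phase of 18 months".
- **Assessments, subsection on the household survey.** The timing is given as follows: "The Endline Household Survey, conducted at months 13–15 after implementation, will be the primary tool to assess the uptake of CCSPT and FP services".

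The survey's place in the calendar is also described in two ways. Aims and objectives puts it at the end of implementation. Design (text under Table 1) puts it near the end of the implementation period. Mixed methods assessments lists months 0–3, 5–7 and 13–15 as the evaluation rounds held during implementation.

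**The concern.** The primary screening outcome carries two stated windows, 12 and 18 months, and the instrument that measures it is used at a time that closes off the longer one. Two things are at stake.

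First, the estimand is not fixed. A 12-month count, a count to the interview date and an 18-month count are different quantities. The text as it stands would let any of them be called the primary outcome after the data are seen.

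Second, the planning rate behind the power statement is attached to 18 months. If less uptake has accrued by the time the survey can observe it, the power figure no longer describes the analysis that will be done.

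**Working it through.** **Step 1: origin of the month count.** Could months 13–15 mean months after implementation has ended? No. Mixed methods assessments uses the same count for rounds held during implementation, and the text under Table 1 puts the survey inside that period. Design leaves only 6 months (dissemination) after implementation, so months 13–15 after its end would fall outside the study. The count runs from the start.

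**Step 2: what the survey can see.** A woman interviewed at month 13 can report 13 months and one interviewed at month 15 can report 15. Between 18 − 15 = 3 and 18 − 13 = 5 months of the stated window are unobserved. A 12-month window is complete for every respondent.

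**Step 3: reproduce the stated power.** Inputs from Sample size calculations: 7 facilities per arm, mean cluster size 3400, ICC 0.15, CV of cluster size 0.35, clinic-only 40%, difference 30 points (40% v 70%), stated power at least 83%. Alpha is not stated; two-sided 0.05 is assumed.

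- Design effect = 1 + ((0.35² + 1) × 3400 − 1) × 0.15 = 573.3
- Effective n per arm = 7 × 3400 / 573.3 = 41.5
- Power = Φ(Δ / √[(p₁q₁ + p₂q₂)/41.5] − 1.96)
- √[(0.24 + 0.21)/41.5] = 0.104; 0.30/0.104 = 2.88; Φ(2.88 − 1.96) = 82.2%

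Replacing CV² by CV² × (k − 1)/k, with k = 7 facilities per arm, gives 82.7%. The stated figure is reproduced to within a point, so its arithmetic is not in question.

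**Step 4: shorter windows.** The documents give no accrual curve. Two assumed shapes show the range, both treating the planning rates as 18-month values:

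- Linear: p × T/18
- Constant hazard: 1 − (1 − p)^(T/18)

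Example, 40% v 70% at T = 12. Linear gives 26.7% v 46.7%, a difference of 20.0 points, and 0.200/0.1035 = 1.93, so power is Φ(−0.03) = 49%. Constant hazard gives 28.9% v 55.2%, a difference of 26.3 points, and 0.263/0.1044 = 2.52, so power is Φ(0.56) = 71%.

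The same formula for other windows and rates gives:

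| 18-month rates | Window | Linear: difference, power | Constant hazard: difference, power |
|---|---|---|---|
| 40% v 70% | 12 | 20 points, 49% | 26 points, 71% |
| 40% v 70% | 13 | 22 points, 54% | 27 points, 74% |
| 40% v 70% | 15 | 25 points, 66% | 29 points, 78% |
| 40% v 80% | 12 | 27 points, 73% | 37 points, 95% |
| 40% v 80% | 14 | 31 points, 85% | 39 points, 97% |
| 50% v 80% | 12 | 20 points, 47% | 29 points, 78% |
| 50% v 80% | 14 | 23 points, 59% | 30 points, 82% |

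The 40% v 70% rows use the smallest difference for which the article claims its power. The 80% rows use the level that the article hopes to approach with community sampling.

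**Step 5: the FP outcome.** The analysis plan defines it as current use of a modern method among women aged 15–50. That is status at interview and is not truncated by the survey date. For FP, the mismatch is that the abstract and the hypothesis speak of services received over a period (18 and 12 months) while the analysis plan measures current use.

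**The case against.** The strongest reply is that this is largely a labelling problem. The survey records screening received during implementation separately from earlier screening, so uptake to interview is measurable in both arms. The 12-month hypotheses and a survey at months 13–15 fit together; only the 18-month label is out of line. Both arms are surveyed in the same period, so the randomised comparison is not biased by the mismatch. Thirty points is the smallest difference powered, not the forecast, and the 18-month period is attached expressly only to the clinic-only 40–50%.

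Most of this stands, and it rules out three stronger readings.

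- *That the endpoint cannot be estimated at all.* Only the 18-month version is out of reach.
- *That field order biases the comparison.* Someone interviewed at month 13 has up to 2 months less exposure than someone at month 15. But nothing in the article says that facilities are visited in sequence or by arm, and enumeration areas are drawn from all catchments. The documents do not support a claim of bias.
- *That the trial is shown to be underpowered.* That depends on an accrual curve nobody has stated. With 50% v 80% and constant hazard, the month-15 difference is still 30.0 points (43.9% v 73.9%). If uptake had levelled off before the survey, the stated power would stand.

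What the reply does not remove is that the analysis plan, the abstract and the sample size section all name a window that the chosen survey date cannot cover.

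**Conclusion.** The point holds for the screening outcome. The text gives 18 months in three places, 12 months in the hypotheses, and a survey date that excludes months 16–18 for every respondent. The 18-month proportion cannot be observed as planned, and the clinic-only planning rate is tied to that period.

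The consequence for power is conditional. At 12 months it runs from 49% to 71% if the 18-month rates are 40% v 70%, and from 73% to 95% if they are 40% v 80%. At month 14, the planning rates of 40–50% v 80% span about 59% to 97%. These figures assume two-sided 0.05, the article's own design inputs and one of two illustrative accrual shapes. They show that the stated 83% does not automatically carry over to the observable window. They do not establish a shortfall.

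For FP the issue is only inconsistent wording, since current use is not affected by the survey date.

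**What to change.** 1. Use one screening window in the abstract, Aims and objectives, Sample size calculations and Analysis plan. Screened within the first 12 months after the facility's start date agrees with the hypotheses and is complete for every woman surveyed at months 13–15.
2. Make sure that the survey dates each screening (month and year), so that the 12-month count can be derived. The questionnaire is not shown and may already do this.
3. Report uptake to the interview date as a secondary outcome.
4. Restate the planning rates for the chosen window, and give power as a range over stated accrual assumptions.
5. Keep the FP outcome as current modern-method use and bring the abstract and the FP hypothesis into line with it.

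The alternative is to run the survey after month 18 and keep the 18-month window.

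The 12-month option costs wording changes, possibly one survey item, and a rerun of the power calculation. Its downside is that fewer screenings are counted and the power figure may be less favourable. The alternative keeps the 18-month planning rates but moves fieldwork into the dissemination phase.

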### Site selection and randomization

In each district, we selected 8 facilities that were representative of the 4 facility types in which our models would most likely be implemented: (1) one central/district hospital, (2) one CHAM hospital, (3) two urban health centers, and (4) four rural health centers. The facilities were chosen in consultation with the District Health Management teams of each district. We evaluated the readiness of each facility to implement our models, excluding those with no existing FP services or laboratories. We discussed potential facilities with other local partners, including other research groups, nonprofits, and international health organizations.

Once the 16 facilities were selected, they were assigned a code. The facilities were then randomized to one of the models in a 1:1 randomization within each of the 4 facility type strata (Table 3) by a UNC Project-Malawi biostatistician, using the facility codes. This randomization resulted in 8 health facilities assigned to model 1 (4 in Lilongwe, 4 in Zomba) and 8 health facilities assigned to model 2 (4 in Lilongwe, 4 in Zomba). However, when we discovered that neither Bwaila District Hospital in Lilongwe nor Zomba Central Hospital in Zomba could be randomized to model 2 given their lack of HSAs (see sample size text above), we determined that we could not include Zomba Central Hospital or Bwaila District Hospital in our analyses to compare model 1 and model 2 (see “Sample size calculations” section). Therefore, we will only be analyzing 14 health facilities for that comparison: 7 assigned to model 1 (3 in Lilongwe, 4 in Zomba) and 7 assigned to model 2 (4 in Lilongwe, 3 in Zomba).

**Table 3 Tab3:** Selected sites with their initially assigned model number, within their health facility stratum

Health facility strata	Lilongwe district	Assigned model	Zomba district	Assigned model
**Central/district hospital**	Bwaila District Hospital	1	Zomba Central Hospital	2^a^
**CHAM hospital**	Nkhoma Hospital	2	St. Luke’s Hospital	1
**Urban health center**	Kawale Health Center	2	Matawale Health Center	2
	Area 18 Health Center	1	Zomba City Clinic	1
**Rural health facility**	Kabudula Rural Hospital	1	Domasi Rural Hospital	2
	Lumbadzi Health Center	2	Namasalima Health Center	1
	Chileka Health Center	2	Ngwelero Health Center	1
	Chiwamba Health Center	1	Likangala Health Center	2

*CHAM* Christian Association of Malawi

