^a^Bwaila District and Zomba Central Hospitals will not be included in the final comparison of randomized arms as these hospitals did not have health surveillance assistants who could provide community-based services for model 2

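### The endline survey still spreads its enumeration areas by catchment size over all 16 facilities, so a sizeable and possibly majority share of the sample falls in two hospital catchments excluded from the comparison of models; reallocating it is a cheap efficiency gain.

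*Protocol article*

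**What the plan says.** All references are to the protocol article.

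- **Frame and allocation (Endline Household Survey, under Assessments).** EAs are drawn at random from every facility's catchment, hospitals included. The allocation rule is: "This random sample will be selected with the number of EAs proportional to the size of the catchment area". The target is stated as "Our target sample size is up to 8000 women aged 15–50 years from the 16 health facility catchment areas", taken from 266 EAs at about 30 households each.
- **Purpose (Table 2).** The survey is listed under objective 1 only, the comparison of the two models.
- **Exclusion (Site selection and randomization).** The two hospitals had no health surveillance assistants able to deliver model 2. "Therefore, we will only be analyzing 14 health facilities for that comparison". The footnote to Table 3 repeats this: "Bwaila District and Zomba Central Hospitals will not be included in the final comparison of randomized arms".
- **Cluster sizes (Sample size calculations).** For the 16-facility design, "we also estimated an average cluster size of 8000 eligible women per health facility and a coefficient of variation of the cluster sizes of 0.35". After the exclusion, "we dropped these 2 hospitals from our sample size calculations and decreased our average cluster size to 3400 eligible women accordingly". The CV stays at 0.35.
- **Outcomes (Analysis plan).** Key outcomes are screening, thermal ablation among treatment-eligible women, and modern family planning use. They are compared between models by logistic regression that accounts for facility clustering and the small number of clusters.

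**The concern.** The power calculation was revised when the two hospitals left the comparison, but the survey allocation was not. Allocation in proportion to size sends most EAs to the largest catchments, and the fall in mean cluster size from 8000 to 3400 suggests that the two excluded hospitals are by far the largest. Women interviewed there add nothing to the randomised contrast.

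What is at stake is precision per interview. The 14 compared facilities share whatever remains, the smallest of them get the fewest EAs, and unequal catchments become unequal survey clusters. The treatment outcome is the most exposed, because its denominator is a small fraction of the women surveyed: those screened, HPV-positive and eligible for ablation.

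**Working it through.** **1. Share of the sample outside the comparison, from the two means.** This assumes that both means cover the same facilities and that catchment size is proportional to eligible women.

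- All 16 facilities: 16 × 8000 = 128,000 eligible women.
- The 14 compared facilities: 14 × 3400 = 47,600.
- The two hospitals: 128,000 − 47,600 = 80,400, or 40,200 each on average; 80,400 / 128,000 = 62.8%.
- Women: 8000 × 0.628 ≈ 5025 in the hospital catchments and 2975 in the rest; 2975 / 14 ≈ 212 per compared facility.
- EAs: 266 × 0.628 ≈ 167 in the hospital catchments and 99 in the rest; 99 / 14 ≈ 7 per compared facility.
- Equal allocation to the 14 alone: 266 / 14 = 19 EAs and 8000 / 14 ≈ 571 women each.

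**2. The same share from the stated CV.** If the CV of 0.35 holds over 16 facilities with mean 8000, two facilities hold most when both have size 8000(1 + a) and the other 14 have size 8000(1 − 2a/14). Then CV² = a²(2 + 4/14)/16.

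- 0.35² = 0.1225, so a = √(0.1225 × 16 / 2.2857) = 0.926.
- Largest share for two facilities: 2 × 1.926 / 16 = 24.1%. The other 14 would then average at least about 6,900, not 3400.
- At 24.1%, about 6,070 women remain for the 14, or about 434 women and 14 EAs each.

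Conversely, 14 facilities at 3400 and two at 40,200 give CV = √[(14 × 4600² + 2 × 32,200²)/16] / 8000 = 1.52, and any spread within the two groups raises it. The means and the CV cannot both describe the same 16 facilities.

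**3. Power for screening, starting with the plan's own figure.** Inputs from the sample size section: 7 facilities per arm, 40% v 70%, intra-cluster correlation (ICC) 0.15, CV 0.35. Two-sided alpha 0.05 is assumed, since none is stated.

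Design effect D = 1 + [(1 + CV²)m − 1] × ICC; SE = √{[0.4×0.6 + 0.7×0.3] × D / (7m)}; power = Φ(0.30/SE − 1.96).

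| Women per facility (m) | CV | D | SE | Power |
|---|---|---|---|---|
| 3400 (the plan's input) | 0.35 | 573.3 | 0.1041 | 82.2% |
| 212 | 0.35 | 36.6 | 0.1053 | 81.3% |
| 571 | 0.35 | 97.1 | 0.1045 | 81.9% |
| 571 | 0 | 86.6 | 0.0987 | 86.0% |

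The first row is within a point of the plan's 83%. A t reference with 12 degrees of freedom lowers every row but keeps the pattern: 75.4%, 74.4%, 75.0% and 79.7%.

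Going from 212 to 571 women per facility therefore adds 0.6 points. The further 4.1 points, to 86.0%, come from setting the CV to 0. That CV term applies when every woman has equal weight. With ICC-based cluster weights, unequal clusters (mean 212, CV 0.35) already give 85.3%, and the gain from equal clusters of 571 falls to 0.7 points.

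**4. Treatment outcome.** Whatever the screening and positivity rates, the number of women in this denominator from the 14 facilities scales with the women surveyed there: 571 / 212.5 = 2.7 times as many under equal allocation if the 63% holds, and 571 / 434 = 1.3 times at the 24% bound. For scale only, the following assumptions are not in the documents: 50–60% of respondents aged 25–49, 40–70% of those screened, and 15–25% of those HPV-positive. They give about 6–22 positive women per compared facility at 212 surveyed, against 17–60 at 571.

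**The case against.** Much of the case for leaving the allocation alone is sound.

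- **The hospital interviews have uses.** The Fig. 1 legend has both hospitals delivering model 1 (9 facilities in all). The cost section takes the number of women screened from this survey, and the Discussion wants implementation assessed in district-level as well as local settings. A reader might infer that most of the sample is wasted. The documents do not support that: these women are lost to the randomised contrast, not to every use. This argues for keeping a hospital sample, but not for letting catchment size set it.
- **The 63% is not a stated figure.** A reader might take it as the plan's own. It follows from two means, one based on data from potential facilities, and the CV given beside the 8000 contradicts it.
- **The primary comparison is not endangered.** A reader might infer that it is underpowered or biased by the allocation. At an ICC of 0.15 the number of facilities governs power, women per facility barely matter, and nothing in the allocation favours either model. The analysis plan does not fix cluster weights, so the CV penalty may be small.
- **Proportional allocation is a standard design.** It is approximately self-weighting for population coverage, and equal allocation gives that up.
- **No catchment sizes are listed.** It therefore cannot be said which compared facilities are smallest, or that they are the rural ones.

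What remains is that the allocation was not revisited after the exclusion, and that the same fieldwork could tell more about the comparison it is listed to serve.

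**Conclusion.** The point holds as an efficiency improvement and is not a must-fix. The 16-catchment frame, the proportional rule and the exclusion are all explicit. The share of the sample outside the comparison is about 63% if the two means describe the same facilities, and at most about 24% if the CV of 0.35 applied to all 16. The document does not allow a choice between these.

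For screening, reallocation brings power from about 81% to about 86% when women are weighted equally, nearly all of it by removing the CV term, and by less than one point if clusters are already weighted. These figures assume two-sided alpha 0.05 and the plan's ICC of 0.15. The more useful gain is in the treatment outcome, with between 1.3 and 2.7 times as many women from the compared facilities at those two shares, and in estimates for small catchments.

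**What to change.** Before fieldwork:

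1. Tabulate the eligible women in each of the 16 catchments, and correct whichever of the means and the CV is wrong.
2. Allocate most of the 266 EAs equally, or nearly so, to the 14 compared catchments. The ceiling is 19 each (14 × 19 = 266).
3. Within a catchment, select EAs with probability proportional to households, so that about 30 households per EA stays approximately self-weighting.
4. Keep a small fixed number of EAs in each hospital catchment for description and for the costing. For example, 18 EAs in each compared catchment uses 14 × 18 = 252 and leaves 14, or 7 per hospital, within the same total.
5. State in the survey section which catchments enter the comparison of models and which are descriptive.

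The cost is a revised EA allocation table, with no extra interviews. The downsides are less precise hospital estimates, and pooled all-catchment proportions that need weighting by catchment size.
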